## 5.7. MASKING TECHNIQUE

Not applicable, since this has an open clinical trial design.

## 5.8. CASE REPORT FORM

Content of the case report form (CRF) is attached in appendix I.

# 6. – SELECTION OF PATIENTS

## 6.1. CRITERIA FOR DIAGNOSING THE STUDY PATHOLOGY

The diagnostic criteria are based in the clinical history, physical examination, and laboratory parameters.

## 6.2. INCLUSION CRITERIA

1. Adult patient having a diagnosis of HIV-1 infection.
2. Antiretroviral therapy started at least 12 months before, always with a HAART combination including 2 NRTIs plus a PI
3. Current HAART combination including 2 NRTIs plus a PI.
4. Maintained undetectable plasma HIV-1 RNA (VL < 50 copies/mL) since the beginning of antiretroviral therapy, for at least 6 months.
5. Absence of suspected or documented resistance mutations in the RT associated to NNRTIs or to any NRTI.
6. Patient having at least one of the following conditions:

- Dyslipemia (LDL cholesterol >130 mg/dL or triglycerides > 350 mg/dL) derived from their current PI regimen or current use of lipid lowering agents due to dyslipemia,
- Antiretroviral-related gastrointestinal disturbances, or
- Low patient’s satisfaction associated with the current regimen posology (BID regimen, ritonavir use, ritonavir intolerance…).

1. Good treatment adherence.
2. Voluntary written informed consent.

## 6.3. EXCLUSION CRITERIA

1. Previous therapy with mono or dual antiretroviral therapies at least 6 months before.
2. Previous antiretroviral treatment failures, treatment interruptions or blips in viral load (VL > 50 copies/mL) at least 6 months before.
3. Acute infections or uncontrolled chronic infection in the 2 months previous to the inclusion.
4. Pregnancy or fertile women willing to be pregnant.
5. Clinically significant malabsorption syndrome within 30 days prior to randomization.

## 6.4. NUMBER OF PATIENTS

The study is going to be carried out in a sample 40 patients: 20 in Control group and 20 in Etravirine group.

## 6.5. SECURITY CRITERIA

The following safety procedures will be implemented:

- HIV-1 RNA levels will be performed in both treatment arms at week 4 of the study and every 12 weeks thereafter up to week 48.
- An interim evaluation will be performed when 75% of subjects reach week 24 of follow-up. The study will be prematurely interrupted at week 24 if the difference in rates of virological failure between study arms is 10% or higher.

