## 5.3. RANDOMIZATION AND STRATIFICATION PROCESS

Patients receiving a triple-drug standard HAART PI-based and will be randomly assigned in a 1:1 ratio:

- To switch from the PI to Etravirine (Etravirine group), or
- Continue with the same regimen (Control group).

No stratification process will be used.

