## 5.4. STUDY DURATION

The total duration of the study will be 72 weeks: 24 weeks for patient inclusion and 48 weeks of follow-up once the last patient is included.

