## 12.2. RESPONSE EVALUATION

The response evaluation is going to be done per-protocol, an interim analysis will be performed will be performed when 75% of subjects reach week 24 of follow-up , the final analysis will be based on patients completing the entire 48 weeks of treatment.

The statistical significance of the longitudinal changes in the HIV RNA viral load and lipid parameters are going to be assessed by the calculation of the slope of decay and compared using t-student, Wilcoxon or Mann-Whitney distinguishing between treatment groups and/or other relevant baseline factor.

HIV RNA viral load is going to be transformed by the log10 and if necessary, other transformations of the data are going to be considered.

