## 12.4. SAMPLE SIZE DESCRIPTION

This is a control-armed pilot study designed to examine the proof-of-concept of switching from a PI to etravirine.

Given the lack of data with this strategy an exploratory close monitored pilot trial with a limited sample size would provide useful information for the confirmation of the hypothesis and the design of future, adequately powered trials.

The study is going to be carried out in a sample of 40 patients (20 patients in experimental group and 20 patients in control group).

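### The interim stopping rule in section 6.5 has no direction, fires on a gap of two patients, and names no set of patients in which to count failures

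*Protocol*

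**What the plan says.** Protocol section 6.5 sets the timing: "An interim evaluation will be performed when 75% of subjects reach week 24 of follow-up". It then sets the consequence: "The study will be prematurely interrupted at week 24 if the difference in rates of virological failure between study arms is 10% or higher". Both stand in a list of safety procedures. No direction, allowance for chance, minimum number of events or analysis set is attached.

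Section 6.4 gives the size ("The study is going to be carried out in a sample 40 patients: 20 in Control group and 20 in Etravirine group"). Section 5.3 says patients "will be randomly assigned in a 1:1 ratio", without stratification. Section 12.4 offers no expected failure rate and justifies the small sample by saying "Given the lack of data with this strategy".

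On the analysis set, section 12.2 begins "The response evaluation is going to be done per-protocol, an interim analysis will be performed". The restriction to patients who complete 48 weeks comes later in that sentence and is attached to the final analysis.

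Section 6.6 makes virologic failure a reason to leave the study and defines it by two consecutive visits above 50 copies/mL. Sections 8.1.1 and 8.1.3 define it by two determinations above 50 copies/mL within one month.

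**The concern.** A safety rule should react to harm from the switch and count the events that show harm. This rule is weak on both counts.

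- **Direction and size.** A difference between arms with no sign is met equally when patients on their unchanged regimen fail more often. In a trial this small, 10% is two patients, which chance alone can produce. A mandatory stop could then end a 40-patient study when the arms are truly equal, or when the switch looks better.
- **Counting set.** The patients the rule most needs to count are those who fail and leave before week 24. If they are left out of the rates, a real excess on etravirine could go unseen. The protocol does not say that they are kept.

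The protocol itself fixes the trigger, the threshold and the consequence, so these are not details it merely leaves to an analysis plan.

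**Working it through.** **Inputs.** N = 40, 20 per arm (6.4); 1:1 allocation (5.3); interim at 75% reaching week 24 and threshold 10% (6.5). The protocol states no failure rate, so a common rate p from 1% to 10% is assumed. It gives no operating characteristic for the rule, so there is no figure of its own to reproduce.

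**Step 1: the threshold in patients.** 0.75 × 40 = 30, about 15 per arm.
- 15 per arm: 1/15 = 6.7% (no stop); 2/15 = 13.3% (stop).
- 20 per arm, if every patient's data are used: 1/20 = 5% (no stop); 2/20 = 10% (stop, because the rule says 10% or higher).

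**Step 2: chance of stopping when the arms are equal.** Let X_E and X_C be independent Binomial(n, p) failure counts. At these sizes the trial stops when |X_E − X_C| ≥ 2, so

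P(stop) = 1 − Σ P(x)² − 2 Σ P(x)P(x+1).

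Worked case, n = 15 and p = 5%: P(0) = 0.4633, P(1) = 0.3658, P(2) = 0.1348, P(3) = 0.0307, P(4) = 0.0049. The squares sum to 0.3676. Twice the adjacent products is 0.4461. P(stop) = 1 − 0.3676 − 0.4461 = 0.186.

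| Common failure rate | 15 per arm, either direction | 15 per arm, etravirine worse only | 20 per arm, either direction | 20 per arm, etravirine worse only |
|---|---|---|---|---|
| 1% | 1.7% | 0.8% | 2.8% | 1.4% |
| 2% | 5.4% | 2.7% | 8.4% | 4.2% |
| 3% | 9.8% | 4.9% | 14.5% | 7.3% |
| 5% | 18.6% | 9.3% | 25.3% | 12.6% |
| 10% | 34.5% | 17.3% | 41.7% | 20.8% |

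With equal arm sizes and equal rates, symmetry makes half of the stops control-worse. A 14/16 split changes little: 18.8% at p = 5% and 34.7% at p = 10%, either direction.

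**Step 3: what a direction costs in detection.** True rates 20% on etravirine and 5% on control, 15 per arm: P(stop) is 67.1% in either direction and 65.9% for etravirine worse only. With 20 per arm: 77.9% and 76.9%.

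**Step 4: what losing early failures would cost.** Assume true rates of 25% on etravirine and 5% on control, and that a share s of failures in each arm drops out of numerator and denominator. The observed rate is p(1 − s)/(1 − ps). At s = 0.5 this is 0.125/0.875 = 14.3% and 0.025/0.975 = 2.6%. With 15 counted per arm, the chance of a stop for etravirine worse is 79% at s = 0, 55% at s = 0.5, 21% at s = 0.8 and 0% at s = 1. The shares are illustrative.

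**Step 5: the event being counted.** Visits are at weeks 4, 12, 24, 36 and 48 (5.6), so scheduled visits after week 4 are 8 or 12 weeks apart. Two consecutive scheduled visits from week 4 on therefore cannot fall within one month. The definition in 6.6 and the one in 8.1.1 and 8.1.3 can classify the same patient differently.

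**The case against.** **A sensitive rule can be deliberate.** Section 12.4 describes a closely monitored exploratory pilot with no power claim. A low threshold trades false stops for early detection, and a safety trigger need not be a significance test. That stands, and it is why the 10% threshold is left alone here. It does not explain why a rule listed for safety should fire when control does worse. A symmetric rule does protect control patients too, so adding a direction is a trade-off.

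**The false-stop chance may be small.** A reader might infer that the rule has a high false-stop probability as such. The documents do not support that without a failure rate. Section 6.2 requires sustained suppression, no suspected or documented resistance to NNRTIs or NRTIs, and good adherence, so 1 to 2% is possible, and the chance is then 1.7 to 8.4% across the two arm sizes.

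**Half the stops favouring etravirine** holds only when the arms are truly equal. At 20% against 5% with 15 per arm, wrong-direction stops are 67.1 − 65.9 = 1.2 percentage points.

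**The per-protocol loss is not stated.** A reader might infer that the interim is computed in a set that excludes failures. Section 6.5 names no set, 12.2 ties completion to the final analysis, and reaching week 24 defines when the interim occurs, not its denominator. Failure is also a planned exit, not a protocol violation, and 8.1.3 counts failures throughout the 48 weeks. What stands is that the set is not fixed and that one available reading loses early failures.

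**Stopping at week 24.** Section 5.4 allows "24 weeks for patient inclusion and 48 weeks of follow-up once the last patient is included". With even accrual the interim falls at calendar week 0.75 × 24 + 24 = 42, when the first patients are past week 24. One might infer that the stop cannot be carried out. Even accrual is an assumption, and the phrase reads naturally as the week-24 interim, so this is only wording.

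**Conclusion.** The point holds in a limited form and should be fixed. It does not invalidate the design. Two parts need no assumed failure rate: the rule has no direction, and 10% is a gap of two patients at both 15 and 20 per arm. The size of the problem does depend on the rate. With equal arms, the chance of stopping is 1.7 to 8.4% at 1 to 2% failure and 18.6 to 41.7% at 5 to 10%, across 15 and 20 per arm. These figures assume independent patients, equal arm sizes and the same true rate in both arms. The loss of early failures is a risk from an unspecified set, not something the protocol prescribes. The two failure definitions leave the count behind the rule ambiguous whichever set is used.

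**What to change.** In section 6.5:

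1. Define the difference as the failure rate on etravirine minus the rate on control, keeping the sponsor's 10% threshold.
2. Compute it in all randomised patients whose week-24 date has passed, including those who have left, and count patients withdrawn for virologic failure as failures. State that the per-protocol set of 12.2 does not apply to this rule.
3. Print the rule in patients (an excess of two or more etravirine failures at 15 or 20 per arm) with its false-stop probability over the assumed range of failure rates. Recompute the number if the arms are unequal: at 12 and 18, for example, 2/12 − 1/18 = 11.1%, so an excess of one patient can trigger it.

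Reconcile the failure definition in 6.6 with that in 8.1.1 and 8.1.3, so that one definition feeds the count.

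The cost is wording in these sections, with no added patients or visits. The trial would no longer stop automatically if control does worse. False stopping is halved, not removed: 9.3% at 5% failure and 17.3% at 10% with 15 per arm, or 12.6% and 20.8% with 20. At 20% against 5% with 15 per arm, the chance of stopping goes from 67.1% to 65.9%.

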## 6.6. WITHDRAWAL AND DROPOUT CRITERIA

The patients will complete the clinical study before the stipulated time in the following circumstances:

- Virologic failure: it is defined as an increase in VL > 50 copies/mL on two consecutive visits.
- Interruption of treatment due to adverse events, intolerance or poor adherence during the study.
- Concurrent process or illness which in the opinion of the investigator requires the withdrawal of the patient.
- The patient does not wish to continue in the study.

If the study must be interrupted prematurely, all of the materials should be returned to the sponsor, at the *Lluita Contra la SIDA Foundation.*

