### 6.6.1. Medical Approach to Withdrawal

In all cases in which the treatment is concluded prematurely for any reason, detailed information will be given about the date and reasons of the discontinuation to the promoter.

The investigator will facilitate the necessary medical support to the patient who discontinues the study prematurely due to treatment failure or to the appearance of an adverse event or a related concurrent illness.

In case of virologic failure,

- Genotypic resistance testing will be performed to all participants experiencing virologic failure during the study.
- A salvage regimen will be optimized according to genotypic resistance testing and previous antiretroviral treatment history.

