# 8.- TRIAL CONDUCTION AND RESPONSE EVALUATION

## 8.1. CRITERIA FOR RESPONSE EVALUATION

### 8.1.1. Principal Study Variable

Viral load at week 48.

Virologic failure is defined as an increase in HIV RNA >50 copies/mL in 2 determinations within 1 month. The first date with VL > 50 copies/mL will be used to calculate time to virologic failure.

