**Secondary objectives:**

To compare the immunological efficacy of etravirine-based regimen with standard PI-containing regimens.

- Changes in CD4+/CD8+ T lymphocytes at week 48 from baseline.

To compare the tolerability and toxicity of etravirine-based regimen with standard PI-containing regimens.

- Changes in lipid parameters (total, HDL-, LDL-cholesterol and triglyceride levels) at week 48 relative to baseline values.
- Changes in the administration of lipid-lowering drugs throughout the study (new administrations or the withdrawal of previous lipid-lowering drugs).
- Percentage of patients who withdraw from the study.
- Percentage of patients who withdraw from the study due to toxicity.
- Percentage of patients with toxicity ≥ grade 3.

To compare the cardiovascular risk of etravirine-based regimen with standard PI-containing regimens.

- Changes in cardiovascular risk estimated by changes in the SCORE equation at week 48 relative to baseline values.

To compare patient’s satisfaction of etravirine-based regimen with standard PI-containing regimens.

- Changes in patient’s satisfaction at week 48 from baseline, using a 100 mm analogue visual scale.

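### Patients who interrupt treatment for adverse events, intolerance or poor adherence leave the study, so week-48 outcomes are lost for outcome-related reasons, possibly unequally by arm

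*Protocol*

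**What the plan says.** Protocol section 6.6 introduces its list with "The patients will complete the clinical study before the stipulated time in the following circumstances". One entry is "Interruption of treatment due to adverse events, intolerance or poor adherence during the study". Virologic failure is on the same list. Stopping treatment for any of these reasons is therefore also the end of participation.

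Section 6.6.1 says what follows a premature stop: "detailed information will be given about the date and reasons of the discontinuation to the promoter". It adds medical support and, after virologic failure, genotyping and a salvage regimen. It mentions no later study visit and no week-48 assessment.

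Section 12.2 sets the analysis population: "The response evaluation is going to be done per-protocol", and "the final analysis will be based on patients completing the entire 48 weeks of treatment".

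The endpoints that need a late value are the principal variable in section 8.1.1, "Viral load at week 48", and in section 8.1.3 the week-48 changes in CD4/CD8, SCORE, satisfaction and lipids, the last worded as "Changes in lipid parameters (total, HDL-, LDL-cholesterol and triglyceride levels) at week 48 relative to baseline values". Section 8.1.3 also counts withdrawals and withdrawals for toxicity, and section 12.3 describes dropout for all included patients.

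**The concern.** The reasons for stopping are close to the outcomes under study. Tolerability and satisfaction are secondary objectives (section 4.2), and Hypothesis 2 (section 4.1) predicts better lipids and satisfaction after the switch. A patient who stops because of intolerance is plausibly less satisfied than one who continues. If such patients have no week-48 value, each arm is summarised by those who managed on their regimen. When the two arms lose different numbers, the comparison is no longer between the randomised groups.

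This cannot be left to a statistical analysis plan. Such a plan could redefine the analysis set, or count stops as failures for the binary virologic endpoint. It could not produce week-48 CD4/CD8, lipid, SCORE or satisfaction values that the protocol does not have collected.

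**Working it through.** The protocol states no figure to reproduce. Section 12.4 fixes 40 patients as a pilot size and gives no dropout rate, power or SD. The figures below are illustrations. The only input taken from the protocol is 20 patients per arm; stop counts, k and the SD are assumptions.

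**Week-48 change scores.** Let f_E and f_C be the fractions stopping on etravirine and control. Let stoppers be k SD worse than completers in either arm. Within an arm, the completers' mean exceeds the mean of all randomised patients by k × f. The bias in the between-arm difference, with a positive sign favouring etravirine, is

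bias = k × (f_E − f_C) in SD units; multiply by 25 mm for satisfaction (assumed SD).

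| Stops, etravirine vs control | f_E − f_C | Bias at k = 0.5 | Bias at k = 1 |
| --- | --- | --- | --- |
| 4 vs 1 | 0.20 − 0.05 = 0.15 | 0.075 SD (1.9 mm) | 0.15 SD (3.75 mm) |
| 6 vs 2 | 0.30 − 0.10 = 0.20 | 0.10 SD (2.5 mm) | 0.20 SD (5.0 mm) |
| 3 vs 3 | 0 | 0 | 0 |
| 1 vs 3 | 0.05 − 0.15 = −0.10 | −0.05 SD (−1.25 mm) | −0.10 SD (−2.5 mm) |

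For scale, the standard error of a difference in means with 20 per arm and SD 25 mm is 25 × √(2/20) = 7.9 mm.

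**Virologic failure.** One patient is 1/20 = 5 percentage points of an arm. Assume no virologic failure among completers, so the completers-only difference is 0. Counting stops as failures gives d = (stops on etravirine − stops on control)/20, with SE = √[p_E(1 − p_E)/20 + p_C(1 − p_C)/20]:

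- 4 vs 1: d = 15 points, 95% CI −5.0 to 35.0; completers 16 vs 19.
- 6 vs 2: d = 20 points, 95% CI −4.0 to 44.0; completers 14 vs 18.
- 3 vs 3: d = 0; completers 17 vs 17.
- 1 vs 3: d = −10 points, 95% CI −28.3 to 8.3; completers 19 vs 17.

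The protocol has no rule that counts stops as failures. The comparison only shows how far two treatments of the same patients can diverge.

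**Direction.** With exact binomial counts at 20 per arm, the probability of more stops on etravirine than on control is 0.90 if the true rates are 20% vs 5%, 0.79 at 15% vs 5%, 0.39 at 10% vs 10%, and 0.08 at 5% vs 15%. The answer follows the assumed rates, and the protocol gives none.

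**The case against.** A reader might infer that the losses fall mostly on etravirine, because only that arm starts a new drug (section 5.3) and everyone has had at least 12 months of therapy including a PI (section 6.2). The completers analysis would then favour the switch. The documents do not support so firm a claim. Section 6.2 also requires dyslipemia or lipid-lowering treatment, gastrointestinal disturbance, or low satisfaction with the current regimen, including ritonavir intolerance. Controls keep that regimen, open label (section 5.7), and could leave as often or more often.

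A larger size is also tempting. If exactly the lowest scorers left, losing 10%, 20% or 30% of the etravirine arm would raise its mean satisfaction by 4.9, 8.7 or 12.4 mm at an SD of 25 mm, from SD × φ(z)/(1 − d). The arithmetic is right. But it is a ceiling for one arm's mean with no loss among controls, and not a between-arm bias.

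Nor does section 6.6 remove every poorly adherent patient. The trigger is an interruption of treatment because of poor adherence. That such patients leave before their viral load rises is possible but not shown.

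Further points carry weight:

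- Withdrawals are counted and described (sections 8.1.3 and 12.3), so intolerance is not hidden.
- Viral load, CD4 and biochemistry are scheduled at every visit, with only CD4 and viral load at week 4 (section 8.3), so earlier values will often exist.
- Part of the harm comes from the completers rule in 12.2, so changing 6.6 alone would not cure it.
- This is a 40-patient pilot, the illustrated bias is smaller than the standard error, and values after a stop would partly reflect the next regimen.

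These limit the claim without removing it. Counting withdrawals does not show how those patients fared, and partial data do not replace the week-48 value. Section 12.4 wants the results to inform the design of adequately powered trials.

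**Conclusion.** The point holds in a limited form. Sections 6.6 and 6.6.1 together end data collection when treatment is interrupted for adverse events, intolerance or poor adherence, and section 12.2 then analyses completers. Week-48 outcomes are lost for reasons plausibly related to those outcomes, and the loss may differ by arm. Its direction and size cannot be determined from the protocol.

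The illustrated bias of 0.075 to 0.20 SD rests on the assumed stop counts, on stoppers being 0.5 to 1 SD worse, and on that gap being the same in both arms. In millimetres it also rests on the assumed SD. Nothing in the protocol shows how strongly stopping relates to lipid, CD4 or SCORE changes, so the satisfaction figures should not be carried over to them. The change is worth making because it is cheap and cannot be made after the data are missed.

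**What to change.** In section 6.6, separate stopping study treatment from leaving the study. Patients who stop treatment keep the already scheduled assessments to week 48 (viral load, CD4/CD8, lipids, the SCORE inputs and satisfaction) unless they withdraw consent. Align section 6.6.1 with this.

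In section 12.2, make the main analysis one of all randomised patients in their assigned arm, and keep the completers analysis as supportive. Both sections must change: 6.6 so that the data exist, and 12.2 so that they are used.

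When treatment is stopped, and what follows, remains the investigator's decision and is not affected.

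The cost is protocol wording, since the visits and tests are already planned for all 40 patients, plus modest effort to retain a few of them: 4 to 8 if 10% to 20% of 40 stop, which is an assumed rate. The other downside is that these patients' week-48 values will partly reflect the regimen that follows. The report should say so and show the completers result beside the main one.
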